# Treatment Outcome Measures

1. Efficacy will be evaluated according to the Response Evaluation Criteria in Solid Tumors (RECIST) 1.1, including CR, PR, SD, PD. ORR (CR+PR), DCR (CR+PR+SD). Efficacy evaluation timepoints: Baseline investigations, specifically, spiral CT or MRI examination (which should remain consistent in subsequent efficacy evaluations), will be done within 3 weeks before treatment, and efficacy evaluation will be performed once at Weeks 4, 8 post-dose, respectively and thereafter once every 8 weeks. In case of disease progression, intolerable toxicity or patient-requested withdrawal, the patient will be allowed to withdraw from the clinical trial.
2. Adverse events will be evaluated using the National Cancer Institute-Common Terminology Criteria for Adverse Events (NCI-CTCAE) Version 4.0 (published on June 14, 2010).
3. Pre-treatment Formalin-fixed paraffin-embedded (FFPE) tumor tissue samples will be collected from each patient to explore efficacy biomarkers.

# IX. Safety Evaluation

The safety endpoints include:

- Incidence of all types of AE
- Mortality and causes of death
- Safety laboratory tests, and where applicable, grading per NCI-CTCAE (Version 4.0)
- Vital signs

Safety measures

Symptoms: General symptoms (fatigue, asthenia, perspiration, flushing, fever, lump “sensation”), nervous system symptoms (dizziness, drowsiness, headache, depression, epilepsy, confusion), cardiovascular system symptoms (tachycardia, bradycardia, thromboembolism chest pain), respiratory system symptoms (cough, shortness of breath, dyspnea, asthma), digestive system symptoms [anorexia, nausea, vomiting, abdominal pain, diarrhea, gastrointestinal perforation), hepatotoxicity (hepatic necrosis, chronic hepatitis, hyperbilirubinemia), lipase and amylase increased, pricking pain of tongue tip], hematological symptoms [anemia, hemorrhage, hematological toxicity (thrombocytopenia, neutropenia)], thyroid function abnormalities (hyperthyroidism/hypothyroidism), skin mucosal symptoms (rash, ulceration, pruritus, congestion, etc.), alopecia, injection site symptoms (red swelling, thermalgia and phlebitis), infusion reactions and other symptoms. Special attention should be paid to the sequential relationship between these symptoms and the investigational drug, and their changing process.

Vital signs and physical examination: Mainly include body height, body weight, body surface area, ECOG score, body temperature, blood pressure, heart rate, and respiratory rate.

Laboratory tests: Mainly include routine blood test (Hb, WBC, ANC, PLT), routine urine test (urine PH, urine protein, urine red blood cell, urine white blood cell), hepatic function (ALT, AST, TBIL), renal function (BUN, Cr), electrolytes (K^+^, Na^+^, Cl^-^, Ca^2+^, Mg^2+^), etc.

Auxiliary examinations: Electrocardiogram, X-ray, ultrasound or CT/MRI, etc.

**9.1 Adverse Event (AE)**

The investigator will be responsible for detecting, recording and reporting various types of events that fit the definition of AE or SAE.

**9.1.1 Definition of AE**

An AE is any adverse medical occurrence in a clinical trial subject administered a pharmaceutical product. In this trial, any adverse medical events that occur since the initiation of investigational drug treatment till 30 days after end of treatment will be deemed as AE, no matter they have a causal relationship with the investigational drug or not.

Note: An AE can therefore be any unfavorable and unintended sign (including a clinically significant abnormal laboratory finding), symptom, or disease temporally associated with the use of the investigational drug (newly emergent disease, or worsening of primary disease); for commercially available pharmaceutical products, may also include absence of expected efficacy after administration (e.g., lack of efficacy), abuse and misuse

Examples of AE include:

- Deterioration of chronic sickness or interrupted onset of original symptoms, including increase in the frequency and/or intensity of symptom onset;
- New symptoms detected or diagnosed after administration of the investigational drug, even if such symptoms may have existed before the initiation of the study;
- Signs, symptoms or clinical sequelae suspected to be caused by interactions;
- Signs, symptoms or clinical sequelae caused by the overdose of investigational drug or concomitant medications (essentially, overdose should not be reported as AE/SAE);
- In case of patient death, the cause of death is AE, and the death is the outcome of the AE.

Examples of AE do not include:

- Medical or surgical procedures (e.g.: endoscopy, appendectomy); conditions that lead to such procedures are AE, but surgical procedures themselves are not AE;
- Circumstances in which no adverse medical event occurs (social and/or allowable to hospitals);
- Premature daily fluctuation of pre-existing disease, or no deterioration of symptoms existing or detected at the beginning of the study;
- On-study sickness/disease, or anticipated progression, signs or symptoms of on-study sickness/disease, unless worse than the subject’s anticipated condition;
- Principally, “lack of efficacy” or “absence of intended pharmacological action” should not be reported as AE/SAE. However, signs, symptoms and/or clinical sequelae caused by lack of efficacy, if meeting the definition of AE or SAE, will also be reported as AE/SAE.

**9.1.2 Definition of Severe Adverse Event (SAE)**

An SAE refers to any adverse medical event that at any dose:

1. results in death
2. is life-threatening

Note: The term “life-threatening” in the definition of “serious” refers to an AE in which the patient was at risk of death at the time of the event. However, it does not refer to an AE which hypothetically might have caused death if it were more severe.

1. requires inpatient hospitalization or causes prolongation of existing hospitalization

- Note: Generally, hospitalization refers to subject’s stay in the hospital or emergency ward (at least overnight stay) for observation or treatment, while such observation or treatment should not be performed in the clinic or outpatient section. Complications which occur during the hospitalization period are AE. If a complication prolongs the existing hospitalization or complies with any other criteria of SAE, the event is serious. Whenever there is any doubt about “hospitalization” or necessity of hospitalization, AE should be considered serious.
- The elective treatment of underlying disease with no aggravation from baseline should not be considered as AE

1. Results in persistent or significant disability/incapacity

Note: The term “disability” refers to significant loss in personal activities of daily living. This definition does not include symptoms of less medical significance such as headache, nausea, vomiting, diarrhea, influenza or accidental trauma (ankle sprain), which will interfere with daily living, but will not cause significant loss of function.

1. is a congenital anomaly/birth defect
2. Medical and scientific judgment should be exercised in deciding whether reporting is appropriate in other situations. For example:

- Important medical events that may not be immediately life-threatening or result in death or hospitalization but may jeopardize the patient or may require intervention to prevent one of the other outcomes listed in the definition above should also usually be considered SAE. Examples of such events include malignancies, allergic bronchospasm that requires emergency treatment in an emergency room or at home, blood dyscrasias or convulsions that do not result in hospitalization, or development of drug dependency or drug abuse. An AE which is considered serious in the health expert’s report (e.g.: be considered to result in functional disorder even not complying with the definition of SAE above) should also be reported as SAE.
- For the purpose of reporting, pathogen transmission caused by the route of study administration should also be considered SAE, and all such reaction should be subject to expedited reporting.

**9.1.3 Disease-related Events or Results Not Considered as SAE**

If an event is a part of the natural course of the disease under study (i.e., disease progression), it should not be reported as SAE. The progression of tumor lesion should be recorded in the clinical evaluation part of the eCRF. Death due to disease progression should be recorded in the “Death Record” page of the eCRF and should not be reported as SAE. However, if a subject’s progression of underlying disease exceeds normal expectations, or if the investigator considers there is a causal relationship between the use of investigational drug treatment or study protocol design/procedure and disease progression, the progression must be reported as SAE. Any newly emergent primary tumor must be reported as SAE.

**9.1.4 Abnormalities of Laboratory Tests and Other Safety Assessments Reported as AEs and SAEs**

Any abnormal findings of laboratory tests (hematology, clinical biochemistry or urine test) or other safety assessments (e.g., electrogram, imaging, measurement of vital signs), including results with abnormal changes from baseline, and examination results which are considered clinically significant by the investigator based on medical and scientific judgment, should be reported as AE or SAE.

However, any important clinical safety assessments related to the underlying disease will not be reported as AE or SAE, unless the investigator considers the assessment results are worse than expectations.

**9.1.5 Time Period and Frequency for Collection of AE and SAE Information**

In this study, the information of all AEs that occur within the period from the administration of the first dose of investigational drug till 30 days after the last dose, regardless of their relationship with the investigational drug, will be collected and recorded in the eCRF.

SAEs related to participation in the study (including prejudicial examinations in the study process or for screening), whether or not related to the investigational drug, will be collected and recorded since the subject’s consent on participation in this study till 30 days after the last dose of the investigational drug.

If considered possibly related to the investigational drug, even SAEs which occur 30 days after the last dose should be reported.

All AEs/SAEs, once occur, will be followed up in a strict manner at each specified visit of the study, investigator’s each contact with the subject, and visits after end of study. The investigator will collect AE/SAE information by asking the standard questions below during the study period and 30-day follow-up period and at each visit:

How are you feeling?

Do you have any (other) medical problems since the last visit?

Do you take any new medicines since the last follow-up/assessment?

**9.1.6 Recording of AE and SAE**

When an AE/SAE occurs, the investigator is responsible for reviewing all documentations related to the event (e.g., progress notes, laboratory tests and diagnostic reports). And then record all AE/SAE related information in the eCRF. The investigator is not allowed to submit the subject’s medical record copy as AE/SAE eCRF report form. However, when the medical record copy of some cases is required, this may happen, in which case, all the subject identifications on the medical record copy should be masked before submission.

The investigator should endeavor to make a definitive diagnosis based on the signs, symptoms and/or other clinical information. The diagnosis, instead of single sign or symptom, should be recorded as AE/SAE.

Any AEs or SAEs occurring during the study period must be recorded in the subject’s case file and corresponding eCRF. Each AE or SAE must be separately recorded. Death due to disease progression should be recorded in the “Death Record” page of the eCRF and should not be recorded as SAE.

If abnormal laboratory findings or other abnormal assessments of clinical significance meet the definition of AE or SAE, the AE eCRF page or SAE eCRF page should be completed as required. A definitive diagnosis (if known), instead of abnormal finding, should be recorded.

**9.1.7 Criteria for Assessing the Severity of AE**

The investigator will assess AEs by referring to National Cancer Institute-Common Terminology Criteria for Adverse Events (NCI-CTCAE) Version 4.0 (Version Date: June 14, 2010, see Annex 4). NCI-CTCAE V4.0 adopts descriptive terminology for reporting AEs. The investigator is required to grade the severity of each AE.

If the severity/intensity of a certain kind of AE is not clarified in this guideline, the investigator can make assessments according to the general definitions of Grades 1 to 5 and based on his/her best medical judgment.

AEs are generally graded as:

Grade 1: mild

Grade 2: moderate

Grade 3: severe

Grade 4: life-threatening or resulting in disability

Grade 5: death related to AE*

If the severity/intensity of a certain AE reaches Grade 4, the investigator must report the event as SAE according to the procedures defined in Section 9.1.11 (see the definition in Section 9.1.2). However, Grade 4 laboratory abnormalities such as anemia or neutropenia will be considered SAE only when they meet the criteria of severity described below.

* Note: It is generally considered that death (defined as Grade 5 per NCT-CTCAE Version 4.0) is the outcome of an event and should be recorded as described below.

In case of death, the leading cause of death (the main cause of death) will be recorded and reported as SAE. “Life-threatening” will be recorded as the outcome of the AE; death should not be recorded as an independent event. Only when the cause of death remains uncertain (e.g.: sudden death, unexplained death) can death itself be reported as SAE.

**9.1.8 Pregnancy**

Pregnancy that occurs in the study period must be recorded in the pregnancy report form and reported. To ensure subject’s safety, pregnancy must be reported to investigator within 2 weeks following its occurrence, and must be followed up to determine the outcome (including early termination of pregnancy) and maternal and infant status. Pregnancy complications and termination of pregnancy for medical reasons must be reported as AE/SAE. Spontaneous abortion must be reported as SAE.

In addition, the investigator must try their best to collect the pregnancy information of a male subject’s female sex partner after study enrollment. Pregnancy information must be reported as described above.

**9.1.9 Judgment on the Correlation between AE and Investigational Drug**

The relationship between the investigational drug and AE or the role of the investigational drug in an AE can be judged according to the following categories and criteria:

1) Not related: Through thorough medical judgment, the AE is caused by other reasons (sickness, environment, etc.);

2) Unlikely related: Through thorough medical judgment, the AE is considered unlikely related to the investigational drug:

- There is no temporal relation between the onset of the AE and the administration of the drug
- The AE may be caused by other factors such as change in the disease course, environment or administration of other therapeutic drugs
- The onset of the AE is unrelated to the known characteristics of the drug
- The AE does not recur or worsen after re-challenge

3) Possibly related: (the first 2 must apply) If through thorough medical judgment, the following conditions are met, the AE is considered possibly related to the investigational drug:

- There is a temporal relation between the onset of the AE and the administration of the drug
- The relationship between the onset of AE and the disease course, environment, toxicity or administration of other therapeutic drugs cannot be excluded
- The AE corresponds to the known characteristics of the drug

4) Related: (the first 3 must apply) If through thorough medical judgment, the following conditions are met, the AE is considered related to the investigational drug:

- There is a temporal relation between the onset of the AE and the administration of the drug
- The AE cannot be explained by the disease course, environment, toxicity or administration of other therapeutic drugs
- After drug withdrawal or dose reduction, the AE disappears or abates, and recurs after re-challenge
- The AE corresponds to the known characteristics of the drug

5) Definitely related: (the first 4 must apply) If through thorough medical judgment, the following conditions are met, the AE is considered definitely related to the investigational drug:

- The AE corresponds to the transient outcome after administration, or drug level is detected in body fluid tissues
- The AE cannot be explained by the subject’s disease course, environment, toxicity or administration of other therapeutic drugs
- After drug withdrawal or dose reduction, the AE disappears or abates, and recurs after re-challenge
- The AE corresponds to the known characteristics of the drug

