**1.3 Adverse reactions:**

a) Gastrointestinal reactions: Diarrhea has resulted in drug withdrawal in about 2% of patients. Diarrhea usually occur within the first 2 weeks of treatment and may result in dehydration with or without renal impairment. Therefore, anti-diarrheal medicinal products (e.g., Loperamide) should be used at first signs of diarrhea. Patients with severe diarrhea (grade 2 or 3 diarrhea persisting more than 48 hours) may require interruption and dose reduction or discontinuation of therapy with afatinib.

b) Skin related adverse events: Rash/ache has resulted in drug withdrawal in about 2% of patients and generally manifests as a mild or moderate erythematous and acneiform rash, which may occur or worsen in areas exposed to sun. For patients who are exposed to sun, protective clothing, and/or use of sun screen is advisable. Early intervention (such as emollients, antibiotics) of dermatologic reactions is recommended. For patients with severe bullous, blistering or exfoliative sin conditions, discontinue afatinib therapy permanently and refer to a specialist with expertise in managing these dermatologic effects.

c) Interstitial lung disease: Interstitial lung disease (ILD) or ILD-like adverse reactions (e.g., lung infiltration, pneumonitis, acute respiratory distress syndrome or allergic alveolitis) are reported in 1.6% of patients treated with afatinib, and 0.4% of them die. Interrupt afatinib therapy in all patients with acute onset and/or unexplained worsening of pulmonary symptoms (dyspnea, cough, fever). If ILD is diagnosed, discontinue afatinib permanently and refer to a respiratory specialist in managing the condition.

d) Hepatic function: Hepatic failure has been reported during treatment with afatinib in 1% of patients. Periodic liver function testing is recommended.

e) Keratitis: Symptoms such as acute or worsening eye inflammation, lacrimation, light sensitivity, blurred vision, eye pain and/or red eye should be referred promptly to an ophthalmology specialist. If a diagnosis of ulcerative keratitis is confirmed, treatment should be interrupted.

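### The causality scale in 9.1.9 leaves no category for an adverse event with other causes excluded and no recurrence on re-challenge

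*Protocol*

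**What the plan says.** Protocol section 9.1.9 defines five categories and states, for the upper three, how many listed criteria must be met.

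- 'Related' ("Related: (the first 3 must apply") needs a temporal relation, no other explanation, and "After drug withdrawal or dose reduction, the AE disappears or abates, and recurs after re-challenge".
- 'Definitely related' needs all four of its criteria. The third is the same abatement and re-challenge item.
- 'Possibly related' ("Possibly related: (the first 2 must apply") needs a temporal relation and "The relationship between the onset of AE and the disease course, environment, toxicity or administration of other therapeutic drugs cannot be excluded".
- 'Not related' needs another cause to be judged responsible.
- 'Unlikely related' lists four items: no temporal relation, another possible cause, no link to the drug's known characteristics, and no recurrence or worsening after re-challenge. It does not say how many must apply.

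Three other places bear on this. Section VII (I) 1.3 says "If ILD is diagnosed, discontinue afatinib permanently" and states the same for severe bullous, blistering or exfoliative skin conditions. Section VII (III) otherwise provides for interruption and resumption at a dose 10 mg lower, in a table headed for drug-related events. Section 9.1.5 says "If considered possibly related to the investigational drug, even SAEs which occur 30 days after the last dose should be reported".

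**The concern.** The re-challenge item is a plain conjunction: the event must abate and must recur. Nothing limits it to patients who were re-exposed. Where the drug is stopped for good, recurrence cannot be observed, so the upper two categories are closed. 'Possibly related' does not catch these events, because it asks for a competing cause to remain open. The gap lies where the causal evidence is cleanest, when the investigator has excluded everything else.

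The investigator must then record a competing cause that he or she has ruled out, ignore a mandatory criterion, or leave the item blank. Different investigators may choose differently. Safety is a secondary endpoint in a single-arm trial, so no control group shows how often similar events occur without the drug, and the investigator's attribution carries weight. The category also decides whether a serious event later than 30 days after the last dose is reported.

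**Working it through.** The plan gives no figure to reproduce. The check sets the definitions in 9.1.9 against the events that the protocol's own rules can produce. Every event below has a temporal relation and is a known effect of the drug.

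| Event | Not related | Unlikely related | Possibly related | Related / Definitely related |
|---|---|---|---|---|
| A. Other causes excluded, abates on withdrawal, no re-challenge | fails: no other cause | meets none of the four items | fails second criterion | fails third criterion |
| B. As A, but fatal at first occurrence | fails | meets none | fails | fails: neither abatement nor recurrence |
| C. As A, but resumed at a reduced dose without recurrence | fails | meets one item, if resumption counts as re-challenge | fails | fails: no recurrence |
| D. As A, but another cause remains possible | fails | meets one item | fits | fails second criterion |
| E. As A, and recurs on re-challenge | fails | meets none | fails | 'Related' fits |

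A and B have no category on any reading of 'Unlikely related'. C has none if all four items are required, and falls to 'Unlikely related' if one is enough.

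A full enumeration gives the same result. For an event with a temporal relation, vary:

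- other cause: responsible, possible or excluded (3)
- abates: yes or no (2)
- re-challenge: recurs, does not recur or not done (3)
- known drug effect: yes or no (2)
- first criterion of 'Definitely related': met or not (2)

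That is 3 × 2 × 3 × 2 × 2 = 72 profiles. Other causes are excluded in 72 / 3 = 24. Of these, only the profiles that both abate and recur reach 'Related', and there are 2 × 2 = 4. The other 24 − 4 = 20 have no category when 'Unlikely related' needs all its items.

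Some of the 20 combine no abatement with recurrence, which can hardly occur. There are 2 × 2 = 4 of them, leaving 16. If a single item were enough for 'Unlikely related', the profiles still without a category are known effects, either without abatement and with no re-challenge (2) or with abatement and no re-challenge (2). These 4 are events A and B.

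These are counts of logical profiles, not of patients. They show where the gap lies, not how often it will be met.

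**The case against.** **Causality is a matter of judgement.** The section says the relationship can be judged by these criteria, through medical judgement, so an investigator would probably record event A as 'Possibly related'. That is likely in practice. It still requires attesting to a criterion that is not met, and it understates the attribution.

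**The list of competing causes includes toxicity.** If this meant toxicity of the study drug, event A would fit 'Possibly related'. But 'Related' requires the same list to be ruled out as an explanation, so the only coherent reading is toxicity from something else.

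**Little is lost.** This stands. Section IX lists incidence of all types of adverse event, deaths and their causes, laboratory tests and vital signs. Section 9.1.5 collects events to day 30 whatever their relationship, and 9.1.10 has all serious events reported within 24 hours. A reader might infer that treatment-related counts will be wrong, but the protocol defines no such count. The late-reporting sentence is also most naturally read as a minimum threshold, although it does not say so.

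**Methods are deferred.** Section 9.1.10 refers to a further document, not shown, for assessment methods. It may give guidance, but the five categories and their mandatory criteria are fixed here.

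**Stronger readings that the protocol does not support.**

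- From the 6.3% to 8% who stopped for adverse reactions in the cited lung cancer trials, a reader might infer 40 × 0.063 = 2.5 to 40 × 0.08 = 3.2 patients without re-challenge. Under VII (III), a patient may stop only after resuming at reduced doses, and so may have been re-exposed.
- From the 1.6% rate of interstitial lung disease, a reader might infer a chance of 1 − 0.984^40 = 0.475 of an unclassifiable case. That is the chance of any case at that rate. The gap opens only if all other causes are excluded, and patients with a history or baseline evidence of the condition are not enrolled.
- A reader might infer that no fatal toxicity can be 'Related'. One that abated, recurred on re-challenge and then proved fatal would meet all three criteria. Only an event fatal at first occurrence is shut out.

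**Conclusion.** The point holds as a fault in the scale as written. An event with clear timing, other causes excluded and no re-challenge fits no category. An event that abates and does not recur at the reduced dose misses both 'Related' categories and may drift to 'Unlikely related'. The causality criteria and the discontinuation and dose-reduction provisions of section VII need to be reconciled. This implies no view on which clinical rule is right.

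The consequence is modest: inconsistent causality records, uncertainty over what counts as drug-related in the VII (III) table, and an unclear trigger for serious events later than 30 days after the last dose. The primary endpoint, objective response rate, is untouched. How many patients would be affected cannot be derived from the document.

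The conclusion assumes that the stated numbers of criteria are binding and that the investigator has truly excluded other causes. Where another cause remains open, 'Possibly related' works as intended.

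**What to change.** Change the wording in three places. No dose or stopping rule changes.

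1. **9.1.9, 'Related', third criterion.** Replace with: *abates after withdrawal or dose reduction where this can be assessed, and recurs on re-challenge if re-challenge at the same dose took place; absence of re-challenge, or non-recurrence at a reduced dose, does not count against relatedness.* Qualify the fourth 'Unlikely related' item in the same way. Positive re-challenge may stay mandatory for 'Definitely related'.
2. **9.1.9, 'Possibly related', second criterion.** Replace with: *other causes may or may not be excluded, and the criteria for Related are not met.* Where another cause is judged responsible, 'Not related' still applies.
3. **9.1.5, late serious events.** Make the trigger *considered at least possibly related (possibly, related or definitely related)*.

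With these changes, events A and B meet 'Related', and so does C, because non-recurrence at a reduced dose no longer counts against it. An event that can be assessed and does not abate, or that does not recur at the same dose, falls to 'Possibly related'. No temporally related event is left without a category.

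The cost is a wording amendment, submitted to the Ethics Committee as section XII requires, with matching case report form guidance. Slightly more events will be classed as related.
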